#### Depressive symptom assessment

Depressive symptoms will be measured by the Depression sub-scale of the Hospital Anxiety and Depression Scale (HADS-D) [47]. The HADS-D includes 7 items that measure depression and are rated on a 4-point scale ranging between 0 (not at all) and 3 (most of the time). Positively worded items are reverse-scored and then added with negatively worded items to create a total sum with a maximum value of 21.

### Exercise intervention

The intervention will involve 12 weeks of supervised, progressive (i.e., intensity increases after midpoint testing based on reassessment of aerobic fitness) HIIT sessions two to three times per week. Participants are allowed to choose and alter their frequency of exercise sessions per week as long as they train a minimum of two times per week. The average frequency chosen by participants will inform preferential frequency for future iterations of the study. HIIT exercise sessions will be manualized and led by exercise leaders (i.e., Drs. [name] and [name]). Staff researchers will provide additional safety and monitoring support during each exercise session and assist with data collection and entry. All personnel will undergo training prior to exercise session data collection to ensure standardized sessions.

The individual HIIT sessions will involve 10 cycles of 60-s intervals at the wattage associated with 90% VO_2peak_ followed by 60 s of active recovery intervals at 15 W, totaling 20 min in length (see Fig. 3) [24, 25]. All exercise sessions will begin and end with a 5-min warm-up and cool-down, respectively. Required power output for each interval of the exercise session will be individualized and completely automated using the SciFit FitKey software. VO_2peak_ from baseline (T1) will be used to determine exercise intensity for weeks 1–6. VO_2peak_ from midpoint (T2) will be used for determining exercise intensity for weeks 7–12. Participants will be encouraged to maintain a stepping rate of ~ 80 steps per minute throughout the exercise session [41]. Heart rate will be measured and recorded every minute to characterize the demands of the protocol. Average wattage and steps per minute will be recorded at the end of each interval minute. RPE will be measured every minute and session RPE will be measured at the end of each session using the Borg CR-10 RPE scale [48].

**Fig. 3 Fig3:**
[figure not shown]
Exercise intervention progression schematics with acute exercise session protocols. *Note*: The figure is modified from [name], Motl, and Fernhall [24]. T1=baseline assessment, T2=midpoint assessment, T3=post-intervention assessment, HIIT=high-intensity interval training, VO_2peak_=peak oxygen consumption achieved at either the baseline or midpoint assessment

### Data analysis

All data will be entered, checked, and analyzed using SPSS Statistics (Chicago, IL). All data will initially be de-identified and checked for normality, outliers, errors, and missing entries. Process, resources, management, and scientific feasibility will be examined via descriptive statistics, percentage, and frequency analyses. The effect of the intervention will be determined using a repeated measures, 1-factor analysis of variance (Time) to identify significant changes over time. Multiple comparisons will be corrected using the Bonferroni correction. Disease type, medication use, symptoms of spasticity, and depression will be described and considered in the reporting of the study results. Overall effect sizes will be expressed as partial eta-squared, and small, medium, and large effects will be interpreted as values of 0.01, 0.06, and 0.14, respectively [49]. Feedback data will be reported via descriptive statistics, percentage, and frequency analysis.

We are defining clear Go/No Go Criteria for advancement to a RCT comparing RSTEP HIIT with MICE such that (1) 80% of participants (i.e., 12 participants) must complete at least 20 of the 24 prescribed sessions (i.e., 83%); this criterion is based on an expected dropout rate of ~ 15% [50]; (2) a clinically meaningful change in aerobic capacity and at least one additional outcome measure is required. Among those who successfully complete the trial (i.e., 83% of prescribed sessions), a half standard deviation improvement is necessary in aerobic fitness and at least one of the following outcomes: physical activity, walking, upper arm function, cognition, fatigue, or depression scores; this criterion is based on the universality of a half standard deviation threshold for detecting changes in health-related outcomes in chronic diseases [51, 52].

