**Methods:**

The study will recruit 15 pwMS-wd. Feasibility will be measured via process, resource, management, and scientific outcomes throughout the entirety of the research study. The secondary, clinically relevant outcomes will consist of a neurological exam, aerobic capacity, physical activity, ambulation, cognition, upper arm function, fatigue, and depression. Outcomes will be assessed at baseline (T1), midpoint (T2, following 6 weeks), and post-intervention (T3, following 12 weeks). The intervention will involve 12 weeks of supervised, individualized HIIT sessions two to three times per week. The individual HIIT sessions will each involve 10 cycles of 60-s intervals at the wattage associated with 90% VO_2peak_ followed by 60 s of active recovery intervals at 15 W, totaling 20 min in length plus 5-min warm-up and cool-down periods.

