**Discussion:**

The feasibility design of the proposed study will provide experience and preliminary data for advancing towards a proof-of-concept study comparing HIIT to moderate-intensity continuous RSTEP for improving clinically relevant outcomes in a randomized control trial design. The results will be disseminated via manuscripts for publication and a report for distribution among the National Multiple Sclerosis Society.

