## Methods

### Recruitment

The study will recruit 15 pwMS-wd (i.e., a PDDS score of 3–6) from areas surrounding Berry College. Berry College is located in a highly accessible, rural area in the northwest of Georgia. We will recruit from areas between Atlanta, GA; Chattanooga, TN; and Birmingham, AL. Participants will be asked to provide their own transportation to Berry College. With regard to the sample population, this study focuses on the effects of HIIT in those with MS who are ambulatory, but report walking impairments, as this represents upwards of 75% of the MS community. Although the proposed range of participants (i.e., PDDS scores of 3–6) is wide, all participants within this range report at minimum gait impairment and at maximum are primarily wheelchair users but are able to walk 25 ft in under 2 min. Using this wide range will allow us to answer our key question, while maximizing our recruitment potential in a rural, likely underserved population. We will examine medication use, symptoms of spasticity, and depression in the study results.

Recruitment will occur through fliers provided to local and regional MS Society chapters, clinics, and doctor’s offices; flyers provided at local and regional MS Society events; advertisements on social media; email communication to the local and regional MS Society participants; and by word of mouth. This study will be described as an opportunity to participate in a study testing physiological and functional responses to exercise in persons with MS. Participants will be asked to contact the laboratory by telephone or email for further information about the study and screening for inclusion. See Fig. 1 for a diagram of participant movement from recruitment through completion of the program and Fig. 2 for the schedule of enrollment, intervention, and assessments.

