### Feasibility metrics

We adopted a feasibility study design aimed at providing experience and preliminary data for advancing to a proof-of-concept study in a RCT [32]. Process, resource, management, and science feasibility outcomes will be used to determine how the study is conducted in addition to identifying any perils or pitfalls that could lead to traps and stumbling blocks in a proof-of-concept RCT [32]. Thus, a single treatment group, repeated measures study design is proposed. No control group will be used because we specifically aim to identify the feasibility and preliminary efficacy of the HIIT exercise protocol alone in pwMS-wd [38].

Process, resource, management, and scientific metrics will be measured throughout the entirety of the research study [28, 32]. Table 1 presents the four different feasibility metrics, the specific outcomes related to each metric, how these outcomes will be monitored and assessed, and how the specific metrics are relevant to future phase II and III studies. In brief, the process feasibility outcomes assess participant recruitment and retention, which will provide optimal recruitment methods, expected recruitment rates, and refusal reasons. The resource feasibility outcomes will evaluate any research-stage-dependent time and resource issues that can occur and provide expected retention rates, barriers to participation, compliance rates, participant experience of the program and outcome assessments, suitability of the proposed setting, staff training needs, and monetary costs to conduct the research and establish areas for cost saving. The management feasibility outcomes identify potential human and data management issues and will provide detailed staff time requirements, highlight considerations for alterations, and detail recommended safety procedures. Scientific feasibility outcomes will examine the safety, burden, and treatment effect of the study. Participants’ experience, burden, and perceptions of intervention appropriateness will be assessed, and the treatment effect will be determined through calculating effect sizes for all of the clinically relevant efficacy outcomes. Effect sizes will also be used for power calculations for a proof-of-concept RCT [28, 32].

**Table 1 Tab1:** Feasibility metrics, proposed methodology, and importance to future research in multiple sclerosis

Metric	Specific outcomes	Outcome assessment	Importance to future phase II and III studies

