**Management** (i.e., data management and safety reporting assessment)	1. IRB approval procedures 2. Time and accuracy in data collection, entry, and checking	1. All Institutional Review Board (IRB) approval procedures will be documented and will include communications between the University IRB and staff, and time from submission of IRB application to approval. 2. Data will be checked for completeness and errors. All time spent collecting, entering, and checking data will be recorded.	1. Details procedural and staff requirements for obtaining ethical approval, compliance, and monitoring. Highlights optimal safety procedures to be implemented. 2. Identifies staff time requirements and highlights considerations for alterations to ensure proper data management.
**Scientific** (i.e., safety, burden, and treatment effect assessment)	1. Adverse events, serious adverse events, and clinical emergencies 2. Participants’ experience, burden, and perceptions 3. Treatment effect	1. Adverse events, serious adverse events, and clinical emergencies will be reported and recorded. A safety plan will be enacted in the occurrence of an adverse event wherein participants will be asked to discontinue the HIIT exercise and cool-down (if currently exercising) and will be required to be free of symptoms for at least 48 h before returning to activity. 2. Participants’ experience, burden, and perceptions of intervention appropriateness will be assessed via a short survey at the end of the intervention. 3. Treatment effects will be determined via effect size and clinical meaningfulness calculations of any change in the efficacy outcome variables.	1. Establishes the safety and feasibility of the intervention and identifies considerations for alterations. 2. Determines the acceptability and highlight considerations for alterations. Identifying compliance will further allow correct conclusions to be drawn from the results. 3. Establishes data for power calculations and projected clinical impact.

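### The plan would power a HIIT-versus-MICE trial with effect sizes from a single arm, but the one index it defines, partial eta-squared for time, holds no estimate of that difference

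*Protocol article*

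**What the plan says.** The Data analysis section tests each efficacy outcome with a one-factor (Time) repeated measures ANOVA and adds: "Overall effect sizes will be expressed as partial eta-squared, and small, medium, and large effects will be interpreted as values of 0.01, 0.06", with 0.14 as the threshold for large. No other effect-size index is named.

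The Feasibility metrics section says the treatment effect will be determined from effect sizes for all efficacy outcomes, and continues: "Effect sizes will also be used for power calculations for a proof-of-concept RCT". Table 1, in its Scientific row, gives the importance of the treatment effect to later studies as: "Establishes data for power calculations and projected clinical impact".

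The Discussion part of the Abstract describes the next trial as a "proof-of-concept study comparing HIIT to moderate-intensity continuous RSTEP". The Data analysis section likewise ties its Go/No Go criteria to an RCT of HIIT against MICE. The present study has no control group (Feasibility metrics; also acknowledged as a limitation in the Discussion). The Background states that there is considerable evidence that MICE benefits clinically relevant outcomes in MS.

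**The concern.** A two-arm trial is sized on the difference between its arms. This study has one arm, and the index it will report measures how far the means at three visits differ from one another relative to within-person error. Three features make that a poor input for the RCT.

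- It says nothing about how much the MICE arm would change, and the document itself expects that arm to improve.
- It also absorbs practice effects and regression to the mean, which would occur in both arms of an RCT and largely cancel there.
- It has no sign. A decline, or a change at the midpoint only, counts the same as improvement.

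Providing data for the step to an RCT is a declared purpose of the design, so a misdirected power input affects one of its main products. A secondary matter is that the index is biased upward in a sample this small, and the fixed labels make no allowance for that.

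**Working it through.** The document gives no power calculation to reproduce, so the checks below start from its design figures.

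**Inputs from the document**
- Sample size 15: "The study will recruit 15 pwMS-wd" (Recruitment).
- A lower size of 12, from the Go/No Go rule: "80% of participants (i.e., 12 participants) must complete at least 20 of the 24 prescribed sessions" (Data analysis). 12/15 = 80%, as stated. The expected dropout of about 15% would leave 15 × 0.85 = 12.75. The document does not restrict the ANOVA to 12 people, so 12 to 15 is a plausible range.
- Three visits: "Outcomes will be assessed at baseline (T1), midpoint (T2, following 6 weeks), and post-intervention (T3, following 12 weeks" (Abstract, Methods).
- Labels 0.01, 0.06 and 0.14.

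**Assumed, not in the document:** two-sided alpha 0.05, 80% power, and true HIIT–MICE differences of 0.1 to 0.4 SD. The value of 0.5 SD for a within-arm change is also an assumption, chosen because the Go/No Go rule uses half an SD as its threshold.

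**1. Using a within-arm change as the between-arm difference**

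Per-arm size for a difference of d SD: n = 2(1.96 + 0.84)²/d². For d = 0.5 this is 62.8, so 63 per arm.

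Power for a true difference δ at 63 per arm: Φ(λ − 1.96) + Φ(−λ − 1.96), with λ = δ√(63/2).

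| True HIIT–MICE difference | λ | Power |
|---|---|---|
| 0.4 SD | 2.245 | 61% |
| 0.3 SD | 1.684 | 39% |
| 0.2 SD | 1.122 | 20% |
| 0.1 SD | 0.561 | 9% |

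(The last figure is 8% if only the correct tail is counted.) The per-arm number depends on whether the outcome is standardised by the raw SD or by the SD of change. These power figures barely do, because they turn on the ratio of true to assumed difference.

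**2. Partial eta-squared when nothing changes**

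With three visits the ANOVA has 2 and 2(n − 1) degrees of freedom. Under no change and sphericity, partial eta-squared follows Beta(1, n − 1). Its mean is 1/n, its median is 1 − 0.5^(1/(n−1)), and the chance of reaching a value c is (1 − c)^(n−1).

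| | n = 15 | n = 12 |
|---|---|---|
| Mean | 1/15 = 0.067 | 1/12 = 0.083 |
| Median | 0.048 | 0.061 |
| Chance of 0.01 or more | 0.99^14 = 87% | 0.99^11 = 90% |
| Chance of 0.06 or more | 0.94^14 = 42% | 0.94^11 = 51% |
| Chance of 0.14 or more | 0.86^14 = 12% | 0.86^11 = 19% |
| Value at which p = 0.05 | 1 − 0.05^(1/14) = 0.193 | 1 − 0.05^(1/11) = 0.238 |

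Simulation (100,000 trials per setting, correlations 0.5, 0.8 and 0.9) agreed with these figures under compound symmetry. Under AR(1) correlation the means stayed at about 0.067 and 0.083, so non-sphericity does not remove the bias.

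**3. Dependence on within-person correlation**

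For true means of 0, 0.25 and 0.5 SD, the squared deviations from their mean sum to 0.125. The population value is 0.125/(0.125 + 2(1 − r)), which gives 0.11, 0.17, 0.24 and 0.38 at r = 0.5, 0.7, 0.8 and 0.9. One and the same clinical change is therefore labelled medium or large according to how repeatable the measure is.

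**The case against.** Several points can be made for the plan, and most of them stand in part.

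- **A reader might infer that null outcomes will usually be called medium.** The figures do not support that. At the planned 15 participants the null median is 0.048, which the scale calls small, and about 58% of null outcomes fall below 0.06. The medium label is right for the mean. Only at 12 participants does the chance of medium or above reach about half.
- **A reader might infer that the labels drive decisions in this trial.** They do not. The ANOVA test stands beside them, so a value of 0.14 at 15 participants would be reported with p of about 0.12. Table 1 also promises calculations of clinical meaningfulness. The Go/No Go rule uses a half-SD improvement, and efficacy is secondary to feasibility.
- **A reader might infer that the RCT is bound to be badly undersized.** The document says effect sizes will be used for power but not how. It does not say the within-arm effect will be entered as the HIIT–MICE difference, and the RCT will need its own justification. Only *could be undersized* is supported. The power table concerns an SD change and is not itself a calculation on partial eta-squared.
- **Dependence on within-person correlation is not in itself a fault for power planning**, because power for a comparison of change also depends on it. It does limit clinical reading and comparison between outcomes.

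None of this supplies the missing quantity: effect sizes are assigned to RCT power, and the only one defined is a one-arm time effect. Acknowledging the lack of a control group does not change that.

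**Conclusion.** The point holds as a weakness in how this study is to inform the next one. The stated power input contains no estimate of the HIIT–MICE difference and no direction, while the comparator is expected to work. How far an RCT sized on it would fall short depends on how much MICE improves, which the document does not quantify. Under the assumptions above, power ranges from about 61% for a true difference of 0.4 SD to about 9% for 0.1 SD.

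The small-sample bias is a valid supporting remark and rests only on the planned design and the usual ANOVA assumptions. The same data can properly supply variability, correlation, adherence and dropout for the RCT. No participant, primary feasibility outcome or Go/No Go decision is affected, so this should be fixed but is not critical.

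**What to change.** In Data analysis: report for each outcome the mean T1–T3 change with its 95% confidence interval, the SD of change and the T1–T3 correlation. If a standardised effect is wanted, give a bias-corrected one with its interval. Do not interpret partial eta-squared by the 0.01, 0.06 and 0.14 labels.

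In Feasibility metrics and the Scientific row of Table 1: state that only SD, correlation, adherence and dropout from this study will feed the RCT sample size, and that the target HIIT–MICE difference will be set in advance on clinical grounds. Replacing one standardised within-arm effect by another would not be enough, since it too would lack the between-arm difference.

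The cost is a few sentences and no new data. The reported effects will look less favourable.

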### Screening, eligibility criteria, and retention

#### Inclusion criteria

Participants who meet the following criteria will be included: (a) age 18–64 years, (b) a self-reported diagnosis of MS, (c) self-reported Expanded Disability Status Scale (EDSS) score < 8.0 or Patient Determined Disability Steps (PDDS) scale score ≤ 7.0, (d) relapse free in past 30 days, (e) willing and able to visit Berry College on three testing occasions and twenty-four training occasions, (f) asymptomatic status for maximal exercise testing, (g) physician approval for undertaking exercise testing, and (h) a self-reported ability to speak, read, and understand English. Participants who do not meet those criteria will be excluded from study participation. Age, self-reported MS diagnosis, relapse status, and willingness to visit Berry College’s campus will be assessed using a simple checklist. Confirmed MS diagnosis will be based on a letter from the participant’s neurologist. Disability status will be determined using the self-reported EDSS and the PDDS scale. Asymptomatic status is defined as one or fewer affirmatives on the Physical Activity Readiness-Questionnaire (PAR-Q). MS verification and medical clearance for exercise testing will be provided by the participant’s physician.

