### Outcome assessments

#### Study testing overview

Baseline, midpoint (e.g., after 12 exercise training sessions), and post-intervention (e.g., after 24 exercise training sessions) testing will be performed at Berry College. All outcome assessors will undergo training prior to data collection to ensure that the final outcomes will be administered using standardized instructions and that the data will be collected consistently across time points. The outcome measures will be manualized and standardized. Midpoint testing will occur following 6 weeks of training. Post-intervention testing will occur following 12 weeks of training. The same specialized equipment for collecting baseline outcome measures will be used at the midpoint and post-intervention assessments. The use of a midpoint testing data point provides a temporal characterization of any outcome changes and may identify any discomforts in the initial stages of the program that might be overcome in the second half of the program. It further allows for modifications to the training stimulus based on any improvements after only 6 weeks of training. These data can ultimately inform therapists about the possible changes to expect if the intervention is successful and integrated into a clinical setting.

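### Go criterion 1 counts 20 of 24 sessions over any period, so surplus early sessions can offset whole missed weeks of a 12-week programme

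*Protocol article*

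**What the plan says.** The programme is described in two ways.

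- **By calendar.** The Exercise intervention section sets 12 weeks of supervised training at two to three sessions per week. "Participants are allowed to choose and alter their frequency of exercise sessions per week", provided they train at least twice. Training intensity is set from T1 for weeks 1–6 and from T2 for weeks 7–12. On assessments, the Study testing overview states: "Midpoint testing will occur following 6 weeks of training. Post-intervention testing will occur following 12 weeks of training".
- **By session count.** Inclusion criterion (e) asks for willingness to attend "three testing occasions and twenty-four training occasions", and the Screening procedure repeats this as 27 visits. The Study testing overview also refers to "midpoint (e.g., after 12 exercise training sessions), and post-intervention (e.g., after 24 exercise training sessions) testing".

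The Go rule in the Data analysis section uses the session count: "80% of participants (i.e., 12 participants) must complete at least 20 of the 24 prescribed sessions (i.e., 83" per cent). Its stated rationale is that "this criterion is based on an expected dropout rate of ~ 15" per cent. The same threshold defines the set for the second criterion: "Among those who successfully complete the trial (i.e., 83% of prescribed sessions), a half standard deviation improvement is necessary" in aerobic fitness and in at least one other outcome.

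No section says by when the 20 sessions must be completed, or that a completer must still be training in the final weeks.

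**The concern.** The session count and the calendar agree only for someone who trains exactly twice a week. Anyone who chooses a third session, even in some weeks, builds up a surplus. Because criterion 1 is a plain total, that surplus can stand in for later weeks in which the participant does not train at all. A person who has left the programme can then be scored as having completed it, under a rule whose rationale is an expected dropout rate.

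This matters because criterion 1 is the main numerical test of feasibility and one of two conditions for moving to a randomised trial. The hypothesis in the Background is that 12 weeks of training is feasible. The count tests that over about ten weeks for some participants and about seven for others. The same definition decides whose data enter criterion 2.

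**Working it through.** **Inputs, all from the protocol article:** 15 participants (Recruitment); at least 12 of them with at least 20 of 24 sessions, and an expected dropout of about 15% (Data analysis); 12 weeks, two to three sessions per week, minimum two (Exercise intervention); 24 training visits (Inclusion criteria).

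**Step 1. The plan's own figures reproduce.** 0.80 × 15 = 12. 20/24 = 83.3%. 15 × (1 − 0.15) = 12.75, so 12 whole participants. 12 weeks × 2 = 24, and 24 + 3 tests = 27 visits. The 24 is therefore the total at the weekly minimum.

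**Step 2. When the threshold is reached.** For weekly frequency f with full attendance, the 20th session falls in week ⌈20/f⌉.

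| Sessions per week | Sessions possible in 12 weeks (12 × f) | Week of 20th session | Whole weeks left |
|---|---|---|---|
| 2 | 24 | ⌈20/2⌉ = 10 | 2 |
| 2.5 on average | 30 | ⌈20/2.5⌉ = 8 | 4 |
| 3 | 36 | ⌈20/3⌉ = 7 | 5 |

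At three per week, 18 sessions are done by the end of week 6, and the 20th is the second session of week 7. Stopping there leaves weeks 8–12 untrained.

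**Step 3. How much surplus is needed.** If k of the first w weeks have three sessions and the rest have two, the total is 3k + 2(w − k) = 2w + k. This reaches 20 when k ≥ 20 − 2w:

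- by the end of week 7, k = 6 of 7 weeks;
- by week 8, k = 4 of 8;
- by week 9, k = 2 of 9;
- by week 10, k = 0.

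The week-7 case needs near-constant training at three per week. Passing by week 8 needs a third session in only half the weeks.

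**Step 4. Effect on the decision.** The threshold is 12 of 15. With 11 true completers (11/15 = 73.3%), one early stopper counted as a success gives 12/15 = 80% and turns No-Go into Go. This shows how sensitive the rule is. It is not a forecast, because the article gives no distribution of chosen frequencies or stopping times.

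**Step 5. Check of a capped count.** Credit each week with at most two sessions, the stated minimum. The credited total after w weeks is at most 2w, so 20 requires w ≥ 10 whatever the frequency. The week-7 stopper has 20 attended but at most 7 × 2 = 14 credited. The week-8 stopper at an average of 2.5 per week has at most 8 × 2 = 16. Neither passes.

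**The case against.** The strongest defence is that 24 has a coherent source. It is the required minimum, 12 × 2, and it appears consistently in the eligibility, screening and Go sections. On that reading a third weekly session is an optional extra, and 20 of 24 is 83% of the required dose for everyone. This explains the number. It does not remove the problem, because the extras still count towards the 20 and can still replace weeks with no training.

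A second defence is that 24 is a cap, so that someone training three times a week finishes in week 8. No section states a cap, and it would conflict with the 12-week programme, T3 after 12 weeks and intensity set for weeks 7–12.

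Two further points stand. An early stopper would be visible elsewhere, since Table 1 lists retention and attrition as separate outcomes and the log books record every completed or missed session. In criterion 2 a participant also needs follow-up testing to contribute a change. Neither point alters how criterion 1 is scored.

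A reader might infer more than the article supports:

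- **That T2 and T3 move to weeks 4 and 8 for those training three times a week, so that the Time factor mixes different weeks.** The session counts in the Study testing overview are given only as examples. The calendar statements there, in the Abstract and in the Exercise intervention section fix testing at 6 and 12 weeks. Testing at weeks 4 and 8 would also need a programme that ends at 24 sessions, which is incompatible with treating a week-7 stopper as five weeks short. What remains is that training amounts at T2 and T3 will differ with chosen frequency.
- **That the bar drops to 67% or 56% of the prescribed sessions.** These are 20/30 and 20/36, and the article never calls 30 or 36 prescribed.

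**Conclusion.** The point holds in a limited form. Criterion 1 is a total without a time condition, applied to a programme defined by calendar weeks with a frequency that participants may vary. Depending on chosen frequency, the threshold can be met in week 10, 8 or 7, and a participant can then miss two, four or five whole weeks and still count as a completer for both criteria. The rule thus does not uniformly test whether 12 weeks of training is sustained, and with a threshold of 12 of 15 a single such participant could decide the outcome.

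This assumes full attendance up to the point of stopping and that the calendar statements govern programme length. If a 24-session programme was intended, the fault becomes a direct conflict between the session-based and calendar-based definitions, and the sections still need reconciling. How often early stopping after a surplus would occur cannot be judged from the article. The case for change is that the rule decides whether a trial follows and costs almost nothing to correct.

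**What to change.** 1. Reconcile the 24-session statements (Inclusion criteria, Screening procedure, Study testing overview, Data analysis) with the 12-week, two-to-three-per-week statements (Study testing overview, Exercise intervention), and define what counts as a prescribed session. Which schedule applies is for the investigators.
2. On the reconciled basis, score criterion 1 so that surplus sessions cannot offset missed weeks. One option is to credit towards the 20 of 24 no more sessions per week than the stated weekly minimum, and to require attendance at T3. This fits the Retention plan, which already confines make-up sessions to the same week. Use the same definition for the completer set in criterion 2.
3. Report the actual week and the cumulative sessions at T2 and T3 for each participant.

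Scoring attended over self-chosen sessions at 83% would be a poorer choice. Participants would set their own denominator, and someone attending 29 of 36 (80.6%) would fail while someone attending 20 of 24 passes. Under the capped count, the person attending 29 of 36 passes however the seven absences fall: the first absence in a week costs no credit, so the most that can be lost is four, leaving 24 − 4 = 20.

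The cost is a change of wording and a different tally from log books already kept. Observed adherence may look slightly less favourable. Because enrolment has begun, the change should be made and dated before adherence data are summarised.
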